**Professional**		
**Lack of adherence to guidelines and clinical inertia related to:*e.g*. Overestimation of care actually delivered, a failure to identify and manage comorbid conditions, unawareness or disagreement with evidence-based goals of care and 'soft reasons' to avoid intensification of therapy**.		
	Usual Quality Improvement Program (UQIP)	Advanced Quality Improvement Program (AQIP)
Clinician education	Distribution of treatment protocol	Distribution of treatment protocol
	Two post-graduate educational sessions	Four post-graduate educational sessions provided by diabetologist (opinion leader):
	Evidence based guidelines	Evidence-based guidelines and principles of shared care
	The use of insulin	The use of insulin
		Patient-centered counseling
		Peer review
	Standard educational materials	Extended educational materials
	----	Inviting PCPs during DCT meetings to discuss patient cases
	----	Providing structured communication forms to PCPs by DCT
	----	Distribution of shared care protocol + referral indication
Feedback	At start and end of project: summary of clinical performance	Every 3 months: summaries of clinical performance
	----	Every three months: benchmarking feedback
Reminders	Clinical reminders at start and end of project	Every three months: Clinical reminders
	----	Every three months: Shared care reminders
**Organisational**		
Lack of office system support and organizational aspects of care related to clinical inertia:*e.g*. Lack of decision support and a team approach to care.		
	Usual Quality Improvement Program (UQIP)	Advanced Quality Improvement Program (AQIP)
Team changes	DCT operating close to regular care	Active instalment of DCT operating under supervision of a diabetologist from a University Hospital
		Diabetes Program manager providing logistic support to PCPs
	----	Introduction of shared care protocol Active encouragement by DCT and scientific team of PCPs to use shared care protocol
	----	Referral arrangements Active encouragement by DCT and scientific team to adhere to referral arrangements
	----	Liaison activities by DCT towards in-hospital DCT in secondary care
	----	Involvement of independent pharmacists
Continuous quality improvement	Quality Assurance Team	Quality Assurance Team

We will use two classification schemes to incorporate all six dimensions of the CCM based on the classification scheme from Shojania and colleagues [54], who defined eleven distinct categories of quality improvement interventions adapted from the Cochrane Effective Practice and Organization Of Care (EPOC) group [55]. These categories are: patient education, promotion of self-management, clinician education, audit and feedback, case management, team changes, electronic patient registry, clinician reminders, facilitated relay of clinical information to clinicians, patient reminder systems, and continuous quality improvement. Five interventions are not included in the service program as they are either integrated in other interventions of the program (*e.g*., the patient reminder system is integrated with physician reminder system) or because of complexity in the Belgian primary health care system (case management, audit, electronic patient registry, and facilitated relay of clinical information to clinicians). The different implementation strategies are derived from an overview by Grol and Wensing [56], who have summarized thirteen important theories and models related to the implementation of change to improve diabetes care. These theories/models relate to individual professionals/patients, the social context, and the organizational and economic context.

### Level one: patient

#### Patient education/promotion of self-management

Both patients in the AQIP and UQIP arms can be referred by their PCP to a DCT to receive a medical assessment by an internist as well as to receive patient education, dietary advice, and examination by an ophthalmologist. This core membership of internists, nurse educators, dieticians, and ophthalmologists reflects the basic requirements of diabetes treatment: nutrition, medication, self-monitoring, self-management, and the management of risk factors [57]. Physicians from both the AQIP and UQIP can ask internists/diabetologists for advice on complex patient cases, with or without patient referral. Educational services and promotion of self-management to patients of the AQIP and UQIP are only provided upon referral of the physician. Nurse educators have received a post-graduate one-year training program on diabetes nursing care. The nurse educator applies individual patient counseling, didactic goal-setting, and situational problem-solving as key educational methods to patients in the AQIP, whereas patients from the UQIP receive services approximating regular care, *i.e*., individual patient counseling. Physicians from both the AQIP and UQIP can consult dieticians for complementary dietary advice or can refer their patients to discuss information on meal algorithms, dietary strategies, and tailoring food intake to meet the patients' lifestyle, motivation, and specific needs [57]. Education on lifestyle changes, identification of barriers to diabetes self-management, and stress management will be provided by a health psychologist to patients in the AQIP-program after physician referral.

Patients in the AQIP can receive additional services, including group educational sessions for both patients and relatives, education at home or at the physician's practice (provided by a traveling educator), structured and printed educational materials from the DCT and community organizations, and free tools for self-monitoring of blood glucose levels.

### Level two: professional

#### Clinician education

Interventions for clinician education include an increased understanding of principles guiding clinical care or awareness of specific recommendations for the patient population using a treatment and shared care protocol, as well as four post-graduate educational sessions based on the Transtheoretical Model of Change [58]. The first session will involve training on the use of evidence-based guidelines and the principles of shared care. A second and a third session will focus on the use of insulin and patient-centered counseling. A fourth session will be set up as a peer review session. Educational messages are delivered, for most part, by a locally well-known diabetologist ('opinion leader') using techniques of group academic detailing [59]. Providing clinical leadership in secondary care is important for PCPs working in an unstructured and thus non-integrated health care environment.

The UQIP will incorporate only the first two sessions. AQIP physicians can attend all four sessions and will also receive extended educational materials. Physicians from both groups will receive accreditation points from a national system for their participation at the educational sessions.

### Feedback

Feedback interventions, provided by a program manager to the physicians, will include summaries of clinical performance of diabetes care delivered to individual patients over a three-month period. AQIP physicians will receive ongoing benchmarking feedback, whereas the UQIP will only receive benchmarking feedback at the start and end of the project. Feedback includes the percentage of a physician's patients who achieve target levels for glycosylated hemoglobin, LDL, total cholesterol and triglycerides, systolic/diastolic blood pressure, an eye and foot examination, aspirin and statin prescriptions, anti-hypertensive medication, smoking status, and weight loss.

### Clinician reminders

Clinician reminders for physicians of the AQIP are combined with quarterly feedback by the program manager and reminders to make use of the DCT if treatment targets are not met. Physicians are asked to remind their patients about upcoming appointments. Patients are asked by the physicians to make use of a diabetes passport in which the appointments are noted together with important treatment results. Physicians of the UQIP do not receive clinician/patient reminders nor do they receive reminders on the use of the DCT.

### Level three: organisational

#### Team changes

Team changes are operationalized in three ways. Initially, a DCT will be installed in two primary care facilities that are run by PCPs. The DCTs will be intensively supervised by a diabetologist from the academic hospital in the project region who provides clinical leadership to the team. All DCT members will receive a 60-hour in-house training program on the use of a shared care protocol, communication skills, and team dynamics. Key elements of the interdisciplinary team include shared leadership with common goals, shared professional identity, and collaborative, rather than consultative, relationships among members [60]. Team members are expected to engage and learn from each other and to attend scheduled meetings. An experienced counselor and a member of the academic project team will oversee the training program. The DCTs operate in support of the PCPs and actively promote referrals to physicians of the AQIP if treatment targets are not met [61]. Fortnightly interdisciplinary meetings will be organized between the members of the DCT who can invite individual physicians from the AQIP to discuss complex patient conditions.

Nurse educators, dieticians, and the health psychologist will meet their colleagues from a university hospital-based diabetes team and the supervising diabetologist on a quarterly basis to exchange experiences and discuss complex patient cases. Internists will meet with the supervising diabetologist every other month to discuss individual patient cases.

Structured, extensive reports will be provided by members of the DCT to the AQIP because PCPs rank standardized, structured correspondence very high [62,63]. Physicians of the UQIP will only receive standard communication forms.

Team changes will also include the active promotion of a diabetes program manager who operates as the central point of referral for the physicians. The program manager will be selected based on the following criteria: strong interpersonal communication skills, the ability to create trust, knowledge of diabetes, and organizational capabilities. The program manager will provide physicians from the AQIP with extended (logistic) support, including physician reminders, providing feedback, liaison activities between the DCT and physicians, organizing group educational sessions, and responding to questions on the study or diabetes-related topics. A project website to facilitate this will be accessible for AQIP and UQIP physicians.

The final team change will be involvement of independent pharmacists in the study. Pharmacists are asked to provide physicians in the AQIP program with medication schemes of their patients upon request. As such, pharmacists can play a more active role in patient monitoring or adjusting medication regimens [64-66].

### Continuous quality improvement

Continuous quality improvement will be assured by an iterative process for assessing quality problems in the implementation of the project, developing solutions to those problems, testing their impacts, and then reassessing the need for further action. For this purpose an interdisciplinary quality assurance team will be established that includes a diabetologist, four PCPs, two nurses, internists, dieticians, and pharmacists. The quality assurance team will be asked to monitor the implementation of the project, as well as evaluate outcome indicators of the project. Meetings will be organized on a regular basis with individual members of the quality assurance team.

### Sample size

The project funding agency requires a sample size of at least one-third of the potential PCPs (n = 379), which would capture roughly 2,500 patients with type 2 diabetes mellitus. This sample size allows 80% power (type II error: 0.20) to detect a 20% relative difference between the intervention arms in the proportion of patients achieving a 10% improvement in any one of the following: blood pressure, total cholesterol, or HbA1c (type I error: 0.05; assumed intracluster coefficient 0.6; [67] for calculation methods).

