### Primary and secondary endpoints

The primary endpoints of the study are the proportion of patients reaching ADA targets for three clinical outcomes: HbA1c < 7%; SBD ≤ 130 mmHg; and LDL-C < 100 mg/dl. Secondary endpoints are the mean improvements in individual values of 12 validated parameters: HbA1c, LDL-C, HDL-C, Total Cholesterol, SBP, DBP, weight, physical exercise, healthy diet, smoking status, and statin and anti-platelet therapy.

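### The stated 80% power refers to a 10%-improvement responder outcome that is not an endpoint of the trial, so it applies to none of the three primary endpoints

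*Protocol article*

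**What the plan says.** The Sample size section starts from a requirement of the funding agency: "at least one-third of the potential PCPs (n = 379), which would capture roughly 2,500 patients with type 2 diabetes mellitus". It then says what that number allows, namely 80% power for a relative difference of 20% between arms. The outcome on which the arms are compared is "the proportion of patients achieving a 10% improvement in any one of the following: blood pressure, total cholesterol, or HbA1c". The remaining inputs are "type I error: 0.05; assumed intracluster coefficient 0.6". No control proportion is given.

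The section on primary and secondary endpoints defines the primary endpoints differently: "the proportion of patients reaching ADA targets for three clinical outcomes: HbA1c < 7%; SBD ≤ 130 mmHg; and LDL-C < 100 mg/dl". The abstract lists the same three targets. (The Methods print SBD and the abstract speaks of systolic differences. The subgroup cut-offs in the Statistical analysis section make clear that systolic pressure is meant.) The secondary endpoints are mean improvements in 12 parameters, total cholesterol among them. The Statistical analysis section tests the evolution of these primary and secondary endpoints and adds subgroups by cut-off value. A 10%-improvement responder is not defined or analysed in any of these places.

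**The concern.** A power figure is a statement about one outcome with one control rate and one effect. Here it is attached to an outcome that the trial never tests. Responding and being at target are different events. A patient whose HbA1c falls from 9.0% to 8.1% has improved by 10% and is still off target. A patient who stays at 6.5% is on target throughout and never improves by 10%. A 20% relative difference in one therefore does not imply a 20% relative difference in the other.

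What is at stake is how the result is read. If target attainment does not differ between the arms, readers may hold that null result against an 80% figure that never concerned it. It is also the only statistical statement offered about what the funder's number can achieve.

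**Working it through.** **1. The two definitions side by side**

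| | Sample size section | Primary endpoints |
|---|---|---|
| Type | 10% improvement | Absolute target reached |
| Glycaemia | HbA1c | HbA1c < 7% |
| Blood pressure | Not specified as systolic or diastolic | Systolic, at most 130 mmHg |
| Lipid | Total cholesterol | LDL-C < 100 mg/dl |
| Structure | Any one of three measures | Three targets |

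HbA1c, total cholesterol and blood pressure are all analysed in some form. Only the 10% dichotomy is not.

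**2. Inputs for the arithmetic**

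- From the article: 2,500 patients, 379/3 = 126.3 physicians, coefficient 0.6, alpha 0.05, 20% relative difference.
- Assumed: equal arms, a two-sided test unless noted, one cluster per physician, and a pooled two-proportion test. Randomization is by practice, so group practices would give larger clusters and, at the same coefficient, a smaller effective size.

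**3. Effective size**

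- Patients per physician: m = 2,500/126.3 = 19.8.
- Design effect: 1 + (m − 1) × 0.6 = 1 + 18.79 × 0.6 = 12.27.
- Effective patients: 2,500/12.27 = 203.7, or n = 101.8 per arm.

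**4. Can the stated 80% be reproduced?**

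Not from the article, because the control proportion is missing. Solving for it, a 20% relative increase reaches 80% power when the control proportion is about 75% (two-sided) or 71% (one-sided). Neither value is in the document, so the 80% can be neither confirmed nor refuted even for the responder outcome.

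**5. What the same inputs give for a single target-attainment endpoint**

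With p2 = 1.2 × p1 and p̄ the mean of the two,

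power = Φ{[(p2 − p1) − 1.96 × √(2p̄(1 − p̄)/n)] / √([p1(1 − p1) + p2(1 − p2)]/n)}.

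Worked for p1 = 0.40 and p2 = 0.48: the null standard error is √(2 × 0.44 × 0.56/101.8) = 0.0696, and the alternative standard error is √((0.2400 + 0.2496)/101.8) = 0.0694. Power = Φ[(0.08 − 0.1364)/0.0694] = Φ(−0.81) = 0.21.

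| Assumed control proportion at target | With 20% relative increase | Power | Difference detectable with 80% power |
|---|---|---|---|
| 30% | 36% | 15% | 19.1 points |
| 40% | 48% | 21% | 19.5 points |
| 50% | 60% | 30% | 19.2 points |
| 60% | 72% | 44% | 18.0 points |
| 70% | 84% | 66% | not computed |

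**6. Does this show which outcome has more power?**

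No. In this calculation power depends on the control proportion alone, whatever the outcome is called, and opposite orderings are easy to construct:

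- If the responder is a composite of three independent measures, each with a 30% rate, its control rate is 1 − 0.7³ = 66% and its power about 56%. A target endpoint at 40% has 21%.
- If each measure is taken separately with a 30% responder rate, power is 15%. A target endpoint at 50% has 30%.

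The article gives nothing with which to choose between these cases.

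**The case against.** Four points can be made on the other side.

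- **The funder fixed the size.** This stands. The responder outcome did not generate the 2,500; the power sentence only says what that number allows. A reader might infer that the sample size was derived from the wrong outcome, and the text does not support that. The defect is in the power statement.
- **An article condenses the full protocol.** Condensing explains missing detail. It does not explain naming a different outcome in one section from the one defined in another.
- **The 'any one' wording may mean each measure separately, not a composite.** This is a fair reading, and it rules out any argument that rests on a high composite rate. On either reading the outcome is still a 10% change and still uses total cholesterol.
- **The low power figures come from elsewhere.** This largely stands. They reflect assumed control proportions and above all the coefficient of 0.6. At a 40% control proportion, a coefficient of 0.06 (a value not in the article) would move power from 21% to 79% with no change of outcome. A reader might infer from the table that the trial is underpowered for its primary endpoints, or less well powered than for the responder outcome. Neither follows. Whether 0.6 is right is a separate question.

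**Conclusion.** The point holds as a contradiction within the article. The 80% is stated for an outcome that is neither a primary nor a secondary endpoint and is not analysed, so the article states no power for any of its three primary endpoints. This conclusion needs no assumption about rates; it follows from the two sections alone.

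Its numerical size cannot be fixed. Under the article's own coefficient and the assumptions listed above, power for a 20% relative increase in one primary endpoint runs from about 15% to 66% as the control proportion goes from 30% to 70%. Those proportions are assumptions, and the range illustrates how much is left open; it does not estimate the trial's power. The consequence is for the interpretation of a null result, not for the validity of the planned estimates or tests.

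**What to change.** In the Sample size section, replace the responder outcome with the three primary endpoints. Keep the funder's requirement and the roughly 2,500 patients as given. For each of HbA1c below 7%, systolic pressure of at most 130 mmHg and LDL-C below 100 mg/dl, state:

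- the assumed proportion at target in the control arm (UQIP), with its source;
- the difference that is detectable;
- the resulting power, with the coefficient used.

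The cost is one rewritten paragraph and a short calculation. Enrolment, endpoints and analyses stay as they are.

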### Randomization and allocation concealment

After recruitment, a researcher not involved in the study and blind to the identity of the practices will perform a randomization (by computer-generated numbers) stratified by practice size (solo/duo/group practice) and the presence or absence of an electronic medical recording system. To minimize the possibility of selection bias, all patients within a cluster will be included. Blinding will be ensured for the participating patients, but is not possible at the physician level.

### Data collection

These practices have no pre-existing registers of diabetic patients. Patients with type 2 diabetes mellitus will be identified using physician memory, searching computerized records, and laboratory lists of patients with increased glycemia or registered glycosylated hemoglobin. Baseline data will be collected over a seven-month period. PCPs will be asked to perform a complete examination and blood analysis at the patient's first visit and to complete a paper form. Identified patients without a visit during the first three months of the project will be invited to participate. The completeness of data capture will be double-checked by a data monitor. Final data will be collected over a seven-month period, with call-backs for non-compliant patients. Patient data sheets include socio-demographic and biomedical data. PCPs will need to indicate whether diabetes is treated by the PCP or in a diabetes clinic.

### Primary and secondary endpoints

The primary endpoints of the study are the proportion of patients reaching ADA targets for three clinical outcomes: HbA1c < 7%; SBD ≤ 130 mmHg; and LDL-C < 100 mg/dl. Secondary endpoints are the mean improvements in individual values of 12 validated parameters: HbA1c, LDL-C, HDL-C, Total Cholesterol, SBP, DBP, weight, physical exercise, healthy diet, smoking status, and statin and anti-platelet therapy.

### Statistical analysis

Statistical analyses will be performed using an intent-to-treat approach with a multilevel model. Linear and generalized linear mixed models will be used to account for the clustered nature of the data, *i.e*., patients clustered within PCPs, and repeated assessments clustered within patients. Such models measure how outcomes change over time within patients and whether these changes depend on patient and/or PCP's characteristics, such as the intervention program or DCT use (see hypothesis two). DCT use is defined as having at least one consultation with a member of the team besides the health psychologist and the traveling educator, which are only available for AQIP patients.

We will use generalized estimating equations (GEE), an extension of the quasi-likelihood approach, to test for differences in the evolution of the primary and secondary endpoints for all patients and within the intervention arms. For binary variables, we use the exponential inverse transformation to obtain the 95% confidence interval for the odds ratio.

Subgroup analyses (see hypothesis one) can distinguish intervention effects using different cut-off values. For HbA1C, three subgroups are defined: patients with HbA1c < 7%; HbA1c ≥ 7% and < 8%; and HbA1c ≥ 8%. For SBP, four subgroups are defined: patients with SBP ≤ 130 mmHg; SBP > 130 mmHg and ≤ 140 mmHg; SBP > 140 mmHg and ≤ 160 mmHg; and SBP > 160 mmHg. For LDL-C, four subgroups are defined: patients with LDL-C < 100 mg/dl; LDL-C ≥ 100 mg/dl and < 115 mg/dl; LDL-C ≥ 115 mg/dl and < 130 mg/dl; and LDL-C > 130 mg/dl.

Linear mixed models with subject-specific intercepts and slopes are used to test whether subject-specific evolutions are related to initial parameters. HbA1c will be transformed logarithmically to meet the parametric assumptions of the statistical models. All analyses will be performed using SAS, version 9.

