**Interventions:**

Primary care physicians will be randomly allocated to 'Usual' (UQIP) or 'Advanced' (AQIP) Quality Improvement Programs. Physicians in the UQIP will receive interventions addressing the main physician, patient, and office system factors that contribute to clinical inertia. Physicians in the AQIP will receive additional interventions that focus on sustainable behavior changes in patients and providers.

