**Primary and secondary analysis:**

Statistical analyses will be performed using an intent-to-treat approach with a multilevel model. Linear and generalized linear mixed models will be used to account for the clustered nature of the data, *i.e*., patients clustered withinimary care physicians, and repeated assessments clustered within patients. To compare patient characteristics at baseline and between the intervention arms, the generalized estimating equations (GEE) approach will be used, taking the clustered nature of the data within physicians into account. We will also use the GEE approach to test for differences in evolution of the primary and secondary endpoints for all patients, and for patients in the two interventions arms, accounting for within-patient clustering.

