Clinical inertia is defined as a lack of treatment initiation or intensification in a patient that is not achieving evidence-based goals of care [24]; this is consistent with the definition of medical errors given by the Institute of Medicine [25,26]. Clinical inertia increases the likelihood of adverse outcomes in a high proportion of patients, but it may take years for poorer clinical outcomes to become apparent [27]. Numerous authors, including those who report on clinical inertia, have defined three principal sources for non-adherence to evidence-based guidelines and clinical inertia: physician factors, patient factors, and office system and organizational factors [28-30]. Physician factors that contribute to clinical inertia include an overestimation of care actually delivered, a failure to identify and manage comorbid conditions, disagreement with evidence-based goals of care and the use of 'soft reasons' to avoid intensification of therapy (*e.g*., patient refusal) [31,32]. Patient factors that contribute to clinical inertia are limited motivation or resistance to adopting lifestyles that support optimal disease care, which stresses the importance of patient empowerment as a cornerstone to high-quality diabetes care [33,34]. Office system and organizational factors that contribute to clinical inertia are the absence of decision support and a team approach to care. These three sources interact in complex ways, and interventions to reduce clinical inertia therefore need to be multifactorial in nature. Here, we describe a study protocol of a cluster randomized trial. We have chosen the physician's practice as the unit of randomization since this was considered the most feasible method of conducting the trial. We plan to compare two different interventions for improving adherence to evidence based guidelines and reducing clinical inertia in primary care physicians.

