## Methods

### Study design

The study is an open pragmatic cluster randomized trial with before/after measurements and two intervention arms. A cluster design is necessary because randomization is performed on a practice level, the intervention happens on the physician level, but a large part of the data are analyzed at the patient level. The implementation period of the trial is 18 months.

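### Practices are randomised, but no analysis described has a practice level: the mixed models stop at the physician and the GEE for endpoint evolution at the patient

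*Protocol article*

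**What the plan says.** Three places in the Protocol article make the practice the randomised unit.

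- Background: "We have chosen the physician's practice as the unit of randomization".
- Study design: "randomization is performed on a practice level, the intervention happens on the physician level".
- Randomization and allocation concealment: the allocation is "stratified by practice size (solo/duo/group practice) and the presence or absence of an electronic medical recording system".

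The Abstract (Interventions) differs: "Primary care physicians will be randomly allocated to 'Usual' (UQIP) or 'Advanced' (AQIP) Quality Improvement Programs".

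For the analysis, the Statistical analysis section specifies linear and generalised linear mixed models and spells out the clustering they account for: "patients clustered within PCPs, and repeated assessments clustered within patients". The Abstract gives the same two levels. It also says that the GEE used to compare baseline characteristics works by "taking the clustered nature of the data within physicians into account", and that the GEE for the evolution of the endpoints accounts for clustering within patients. The Statistical analysis section mentions the GEE for evolution again but names no cluster for it.

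The Sample size section gives an intracluster coefficient of 0.6 without saying whether the cluster is the physician or the practice.

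**The concern.** In a cluster randomised trial the arm effect has to be judged against the variation between the units that were randomised. The duo and group strata show that practices with more than one physician are expected. Physicians in such a practice always fall in the same arm. A model whose highest level is the physician counts them as independent replicates of that arm, and a model that clusters on the patient goes further in the same direction.

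If patients of different physicians in one practice resemble each other, because of shared organisation, catchment or habits, the standard error of the arm effect is too small, the confidence interval too narrow and the type I error above the stated 0.05. This touches the arm comparison on all three primary endpoints.

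**Working it through.** **Plan's own figure.** The Sample size section claims 80% power. One third of 379 physicians is about 126, and 2,500 / 126.3 gives m = 19.8 patients per physician. At the stated coefficient of 0.6 the design effect is 1 + 18.8 × 0.6 = 12.27 and the effective sample about 204 patients. The control proportion is not given, so the 80% can be neither confirmed nor refuted. The article gives no figure at practice level. Only m and the 0.6 are carried forward.

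**Levels side by side.**

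| Element | Highest level stated |
|---|---|
| Randomisation (Background, Study design, Randomization) | practice |
| Mixed models (Abstract, Statistical analysis) | physician |
| GEE, baseline comparison (Abstract) | physician |
| GEE, endpoint evolution (Abstract) | patient |

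**Formula for a comparison at one time point.** Split the total variance (set to 1) into practice, physician and residual parts. The correlation of physician means within a practice is

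rho = s²(practice) / [s²(practice) + s²(physician) + s²(residual)/m].

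Let E[d] be the average, over physicians, of the number of physicians in their practice. Ignoring the practice level understates the variance by

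VR = 1 + rho × (E[d] − 1),

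and a nominal two-sided 5% test has actual size 2 × [1 − Φ(1.96/√VR)].

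**Assumptions, none of them in the article.** Mix A puts 50/25/25% of physicians in solo/duo/three-physician practices, so E[d] = 0.5×1 + 0.25×2 + 0.25×3 = 1.75. Mix B puts one third in each, so E[d] = 2. The total ICC is 0.05, or the stated 0.6. The practice-level share of it is a half or all.

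Worked line (ICC 0.05, half at practice level): rho = 0.025 / (0.05 + 0.95/19.8) = 0.025/0.098 = 0.255. Mix A: VR = 1 + 0.255 × 0.75 = 1.19. Mix B: VR = 1 + 0.255 × 1 = 1.26.

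| Total ICC | Share at practice | rho | Mix A: VR, type I error | Mix B: VR, type I error |
|---|---|---|---|---|
| 0.05 | half | 0.255 | 1.19, 7.3% | 1.26, 8.0% |
| 0.05 | all | 0.510 | 1.38, 9.6% | 1.51, 11.1% |
| 0.6 | half | 0.484 | 1.36, 9.3% | 1.48, 10.8% |

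If all practices are solo, E[d] = 1, VR = 1 and the type I error stays at 5.0%.

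**Simulation check.** With 126 physicians, 20 patients each, allocation by practice stratified by size and 5,000 runs per setting, a physician-level t-test rejected in 7.0 to 11.5% of runs for mixed practices and 4.7 to 5.2% for all-solo practices. Clustering on practice gave 4.8 to 6.1% for mixed practices.

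**Analysis of change.** For an arm-by-time effect, stable differences between practices largely cancel. The same formula applies, but rho becomes the practice-by-time share of the variance of the physicians' mean changes. The article gives nothing from which to estimate it. At rho = 0 there is no inflation.

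**The case against.** **The full protocol or analysis plan may handle this.** That would be a good answer to silence. Here the article lists the levels of the hierarchy explicitly, and the list ends below the unit it randomises. An analysis plan that followed the text would build the wrong model. The objection does not remove the point.

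**The size is not established.** This stands. The trial is a before/after design and its models concern change within patients, so a cross-sectional formula only illustrates. The practice mix and the practice-level share are assumptions. A reader might infer a much larger error: if every practice held three physicians, with the ICC at 0.6 and half of it between practices, VR would be 1.97 and the type I error 16.2%. The article does not support that, because solo practices are a named stratum and the level of the 0.6 is not stated.

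**The programme acts on physicians, not on practices.** Sessions, feedback and reminders do go to physicians, and the team changes are mostly external to the practice. So the strength of correlation within practices is plausible rather than shown. Shared allocation is a fact of the design all the same.

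**The GEE for evolution may test change within arms rather than compare arms.** The wording allows that reading. The remedy is therefore framed for every GEE that compares arms.

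**The stratification factors.** A reader might infer that leaving practice size and record system out of the models is part of the same error. It is not. The list of characteristics in the Statistical analysis section is open, such covariates are commonly left to an analysis plan, and omitting them mainly costs precision. It does not make physicians look independent.

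**Conclusion.** The point holds on the text. The randomised unit is the practice, multi-physician practices are expected, and no analysis described has a practice level. The standard error of the arm effect is too small wherever practices differ.

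The size is open. It runs from no inflation (all practices solo) to an illustrative type I error of about 7 to 11% in a cross-sectional comparison, under the two assumed practice mixes and the variance shares shown. Smaller practice-level shares give less and larger groups give more. For the analysis of change it depends on practice-by-time variance, which is unknown.

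The Abstract's wording on allocation should not be read as evidence that physicians were the randomised unit. Three places in the main text say otherwise, so this is an editorial inconsistency to align.

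The correction should be made before analysis: it protects the primary comparison and needs no new data.

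**What to change.** - **Mixed models:** add a random intercept for practice above physician, and a practice-by-time term where change is analysed.
- **GEE:** use practice as the cluster for the robust variance in every GEE that compares arms, including the baseline comparison.
- **Degrees of freedom:** base them on the number of practices, and state that number.
- **Abstract:** say that practices are allocated, as in Background, Study design and Randomization.
- **Secondary recommendation:** include practice size and electronic record system as fixed effects. They are known for every practice from the randomisation.

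The cost is wording, slightly fewer degrees of freedom and slightly wider intervals. For example, 126 physicians under Mix B form 42 + 21 + 14 = 77 practices. With two arms, the two-sided 5% critical value moves from 1.98 (124 degrees of freedom) to 1.99 (75). Any wider interval beyond that is uncertainty that the physician-level model leaves out.
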